## Abstract

**Background:**

Iron deficiency is common in pregnancy. If left untreated, iron deficiency can lead to iron deficiency anaemia, which is a condition related to maternal and neonatal morbidity. The prevalence of iron deficiency increases through the trimesters, which means that women with iron deficiency in the beginning of pregnancy also have a great risk of developing iron deficiency anaemia during pregnancy. Standard treatment is oral iron in individualised intensified doses based on screening values in 1st trimester.

Maternal symptoms of iron deficiency and iron deficiency anaemia include fatigue, reduced physical performance, and restless legs syndrome (RLS). Severe anaemia may cause dizziness, dyspnea, palpitation, orthostatism, and syncope, and it decreases the woman’s ability to cope with blood loss during delivery. The anaemia may also compromise contractility in the uterine musculature increasing the risk for prolonged labour, caesarean section, and postpartum haemorrhage. Foetal iron deficiency may cause low birthweight and adversely affect foetal and early childhood brain development with long-term deficits.

**Methods:**

In this randomised comparative, open-label, single-centre, phase IV trial, 200 pregnant women between 14 and 21 weeks of gestation who have iron deficiency after 4 weeks of standard treatment will be randomised 1:1 to either a single 1000 mg dose of intravenously administered ferric derisomaltose/iron isomaltoside 1000 or a fixed dose of 100 mg oral ferrous fumarate containing 60 mg ascorbic acid.

The primary endpoint is to prevent iron deficiency anaemia defined by a low level of haemoglobin throughout the trial. Other endpoints include other haematological indices of iron deficiency and anaemia, clinical outcomes by questionnaires, and collection of adverse events. Explorative endpoints by medical record follow-up include complications up to 7 days after delivery.

**Discussion:**

This trial will provide evidence on how to prevent iron deficiency anaemia. The trial population represents a clinical reality where pregnant women often have sustained iron deficiency despite an increased oral iron dose. Thus, this evidence can be used to consider the optimal 2nd line of treatment in iron-deficient pregnant women.

**Trial registration:**

European Union Drug Regulating Authorities Clinical Trials Database 2017-000776-29. Registered on 3 May 2017.

ClinicalTrials.gov NCT03188445. Registered on 15 June 2017.

## Administrative information

Note: the numbers in curly brackets in this protocol refer to SPIRIT checklist item numbers. The order of the items has been modified to group similar items (see http://www.equator-network.org/reporting-guidelines/spirit-2013-statement-defining-standard-protocol-items-for-clinical-trials/).

## Introduction

### Background and rationale {6a}

Untreated iron deficiency (ID) in pregnancy can lead to iron deficiency anaemia (IDA) [1, 2]. ID in pregnancy is defined by low iron stores, measured by a level of circulating ferritin < 30 μg/L [3–6]. Iron is essential for basic cellular processes, such as cell division and the synthesis of haemoglobin (Hb) [7]. Anaemia in pregnancy is defined by a Hb level < 11.0 g/dL, WHO [1, 5]. Thus, IDA in pregnancy is defined as Hb < 11.0 g/dL and serum-(*s*)-ferritin < 30 g/μg/L.

In Danish pregnant women, who do not take iron supplementation, approximately 50% have ID and 21% have IDA [8]. Anaemia (regardless the cause) is estimated to occur in 24% of Danish pregnant women (WHO).

The prevalence of ID is approximately 7% in 1st trimester, 14–40% in 2nd trimester, and 30–62% in 3rd trimester [9, 10]. Prevalence of IDA is approximately 2% in 1st trimester, 8% in 2nd trimester and, 27% in 3rd trimester [11, 12]. The steep increase in ID and IDA through the trimesters illustrates that women with ID in the beginning of pregnancy have a great risk of developing IDA during pregnancy.

National recommendations on routine iron supplementation in pregnancy do not necessarily prevent ID and IDA as seen in a Swizz study, where approximately 32% of pregnant women in 2nd trimester had ID and 6.2% IDA despite a recommended daily oral iron dose of 80 mg [13].

Maternal symptoms of ID and IDA include fatigue/exhaustion, reduced physical performance, restless legs syndrome (RLS), and decreased ability to cope with blood loss during delivery. Severe anaemia may cause dizziness, shortness of breath, palpitation, orthostatism, and syncope [14, 15]. Iron is an essential part of myoglobin, which explains why ID may compromise contractility in the uterine musculature that in turn may increase the risk for prolonged labour, caesarean section, and postpartum haemorrhage [16, 17]. The consequence of maternal anaemia for the foetus is low birthweight, which can complicate the neonatal period [18–21]. ID during foetal life may adversely affect brain development with long-term deficits. One trial showed that maternal anaemia in pregnancy could be linked to 14% of cases of mental retardation at a 7-year follow-up [22].

Thus, isolated ID can be symptomatic and adversely affect foetal brain development. ID is a precursor for IDA, which is associated with maternal and foetal/neonatal morbidity. If treated early in pregnancy, the consequences of ID can be prevented.

In clinical practice, the standard treatment of ID and IDA in pregnancy recommended by the Danish Society of Obstetricians and Gynaecologists (DSOG) is oral iron supplementation in individualised doses based on screening values of Hb and ferritin in 1st trimester [23].

Oral iron supplementation is associated with gastrointestinal adverse effects, affecting patient compliance [14]. Thus, not all women treated with oral iron will respond to or comply with treatment. The recommendations are not clear on how to act in case of failure of the standard treatment. Thus, a pregnant woman with sustained ID will most likely be recommended to remain on oral iron and only receive intravenous (IV) iron if she becomes anaemic. However, it has not yet been investigated what treatment—intensified oral iron or IV iron—is most favourable in case the recommended standard treatment is not sufficient.

Treatment with intravenous ferric derisomaltose/iron isomaltoside 1000 (FDI) (Monofer®/Monoferric®, Pharmacosmos, Holbaek) is indicated when oral treatment is ineffective and when rapid iron delivery is clinically indicated. FDI is one of the newer IV iron formulations available. It was initially launched in Europe in 2010 and consists of iron and a carbohydrate moiety where the iron is tightly bound in a matrix structure. It is the matrix structure that enables a controlled and slow release of iron to iron-binding proteins, avoiding potential toxicity from release of labile iron [24]. FDI has been studied in non-clinical reprotoxicology trials. In supra therapeutic doses, foetal malformations were seen in rabbits [Monofer® Investigators Brochure]. The risk for teratogenic or foeto-toxic effects is considered minimal at the proposed therapeutic dose. Several studies of FDI treatment of iron deficiency anaemia have been published without detected unexpected safety issues [25–31]. FDI should be confined to second and third trimester if the benefit is judged to outweigh the potential risk for both the mother and the foetus [6, 32, 33].

Ferrous fumarate containing ascorbic acid denotes a combination product administered in a film-coated tablet for oral ingestion. Ferrous fumarate is a ferrous salt. Ascorbic acid (vitamin C) facilitates iron uptake by maintaining iron in its ferrous form [34, 35].

Previous trials have investigated the use of different IV iron preparations in pregnant women with IDA [36–42]. We have not been able to identify trials investigating the use of IV iron for prevention of IDA in iron-deficient pregnant women. A recent trial where pregnant women with IDA were treated with the IV iron formulation ferric carboxymaltose reported a statistically significant improvement in Hb change from baseline in the IV iron group compared to oral iron group at 6 weeks. Overall hypersensitivity reactions were rare, IV iron treatment had a beneficial effect on Hb increase, and neonatal outcomes did not differ between groups [40].

There are several reasons why it is important to systematically investigate if the use of IV iron is an effective and attractive mode of treatment in pregnancy compared to intensified oral iron treatment in women with sustained ID despite standard treatment: ID rarely resolves despite standard treatment, is unlikely to resolve later in pregnancy if still present after 4 weeks of standard care, is often left untreated in cases of intolerance to oral iron, is unfavourable for the foetus, and can progress into severe ID and IDA in later trimesters.

Therefore, measures to effectively treat ID early to prevent IDA are of great clinical importance.

### Objectives {7}

In order to prevent IDA throughout the trial in pregnant women, who have ID after 4 weeks of standard treatment, the primary objective is to compare the efficacy of a single dose of IV administered FDI with a fixed dose of oral ferrous fumarate containing ascorbic acid.

The secondary objectives are to compare the effect of IV FDI and oral ferrous fumarate with ascorbic acid on (i) haematological indices of IDA in maternal blood, (ii) maternal fatigue and quality of life (QoL), (iii) RLS, (iv) the need for an additional IV FDI dose or (rescue) red blood cell (RBC) transfusion, and (v) safety.

### Trial design {8}

The trial is a randomised, comparative, open-label, single-centre, phase IV trial, with planned 200 women randomised 1:1 to a single dose of IV FDI or a fixed dose of oral iron ferrous fumarate with ascorbic acid. The randomisation is stratified by Hb value (≥ or < 11.0 g/dL).

## Methods: participants, interventions, and outcomes

### Study setting {9}

The trial is being conducted at the Department of Obstetrics and Gynecology at Copenhagen University Hospital, Amager-Hvidovre Hospital, which is a tertiary hospital with 7000–8000 yearly deliveries.

Healthy women who wish to participate and fulfil the inclusion criteria are enrolled at gestational age (GA) 14 + 0–21 + 0. The duration for each participant is approximately 18 weeks and involves four follow-up visits by a trial investigator at the Amager-Hvidovre Hospital.

### Eligibility criteria {10}

Pregnant women at GA 14 + 0–21 + 0 are eligible for inclusion if they fulfil the following criteria: *s-*ferritin < 30 μg/L (0–29 μg/L) after 4 weeks of standard treatment, age ≥ 18 years, and signed informed consent form.

The exclusion criteria are as follows: multiple pregnancies; history of anaemia not caused by iron deficiency; iron overload or disturbances in utilisation of iron; previous hypersensitivity to IV iron or to any excipients in the investigational drug products; active asthma within the last 5 years; multiple allergies; known decompensated liver cirrhosis or active hepatitis; active acute or chronic infections (assessed by clinical judgement); rheumatoid arthritis with symptoms or signs of active inflammation; treated with IV iron products, blood transfusion, or erythropoietin within 4 weeks prior to inclusion; participation in any other interventional trial where the trial drug has not passed 5 half-lives prior to inclusion; any other medical condition that, in the opinion of the investigator, may cause the participant to be unsuitable for the completion of the trial or place the participant at potential risk from being in the trial; meeting RBC transfusion criteria (Hb ≤ 6.9 g/dL = ≤ 4.3 mmol/L with intolerable symptoms of anaemia or an Hb ≤ 6.4 g/dL (≤ 4.0 mmol/L) regardless of anaemia symptoms; and inability to read and understand the Danish language.

### Who will take informed consent? {26a}

Trial investigators will obtain informed consent.

### Additional consent provisions for collection and use of participant data and biological specimens {26b}

On the consent form, the participants will be informed about the use and storage of personal data collected during their participation in the trial, i.e. until completion of trial or withdrawal of consent, this in accordance with the General Data Protection Regulation (GDPR). The consent form contains information concerning the personnel who can access personal data collected during this trial, i.e. investigators, monitor, and regulatory authorities.

By signing the informed consent form, the participants agree to the terms addressed in the form.

This trial involves collecting biological specimens for storage.

## Interventions

### Explanation for the choice of comparators {6b}

The choice of the comparator is based on current standard treatment of ID in pregnancy.

### Intervention description {11a}

A.IV FDI administered at the baseline visit as a single dose of 1000 mg (if pre-pregnancy body weight < 50 kg then 20 mg/kg pre-pregnancy body weight). The dose is diluted in 100 ml 0.9% sodium chloride and is given over approximately 20 min.B.Fixed dose oral ferrous fumarate (100 mg elemental iron) with ascorbic acid 60 mg [34], once daily.

### Criteria for discontinuing or modifying allocated interventions {11b}

If the participant has IDA at *T*_6w_ or *T*_12w_ defined as Hb < 11 g/dL and *s-*ferritin < 30 μg/L, an additional dose of IV iron isomaltoside is allowed in both groups (not at *T*_18w_ due to lack of AE monitoring). The maximum cumulative dose is set to 2000 mg for the individual participant.

### Strategies to improve adherence to interventions {11c}

Compliance to oral treatment is encouraged at every follow-up visit.

### Relevant concomitant care permitted or prohibited during the trial {11d}

Iron supplementation other than study treatment is prohibited.

### Provisions for post-trial care {30}

There is no anticipated harm and compensation for trial participation. Post-trial, the pregnant women will be cared for in a clinical setting, i.e. standard antenatal care, where both intervention and comparator therapies are available.

### Outcomes {12}

The primary endpoint of this trial is a Hb ≥11.0 g/dL (≥ 6.8 mmol/L) at all trial visits post-baseline (*T*_3w_, *T*_6w_, *T*_12w_, and *T*_18w)._

The secondary endpoints are Hb ≥ 11.0 g/dL (≥ 6.8 mmol/L) at each follow-up visit, change in Hb and other haematological indices of ID/IDA from baseline to each follow-up visit (e.g. reticulocytes, reticulocyte haemoglobin content (CHr), *s*-ferritin, *s*-transferrin, *s*-iron, hepcidin, and calculated transferrin saturation (TSAT)), incidence of hypophosphatemia (defined as serum [*s*]*-*phosphate < 2 mg/dL) from baseline to each follow-up visit, change in fatigue and quality of life questionnaires from baseline to each follow-up visit, presence of RLS at each follow-up visit, number of participants who receive an additional IV iron isomaltoside dose at *T*_6w_ and/or *T*_12w_, reason for the additional IV iron isomaltoside dose (non-compliance, lack of effect), number of participants receiving RBC transfusions and the number of RBC units per transfused participant from baseline to final subject visit, type and incidence of AEs observed at any time until final subject visit, serious or severe hypersensitivity reaction starting at or after the first dose of randomised treatment, AEs of special interest (constipation, diarrhoea, flatulence, nausea, vomiting, abdominal pain, dyspepsia, dysgeusia, and stool discoloration), number of participants who discontinue from the trial because of lack of response or intolerance of investigational drugs, foetal bradycardia related to infusion of IV iron isomaltoside at or after GA 26, change in biochemical safety parameters from baseline to each follow-up visit, and compliance to treatment: at baseline in the IV group and at *T*_6w_ and *T*_18w_ in the oral group.

Specific explorative endpoints registered between final subject visit up until 7 days postpartum will be extracted from medical records: incidence of maternal antepartum haemorrhage, thromboembolic events, gestational diabetes mellitus, gestational hypertensive disorders, blood transfusions, prolonged labour, length of labour, oxytocin use, assisted delivery, unplanned caesarean section, postpartum haemorrhage, maternal blood loss at labour (ml), length of maternal and neonatal hospital admission, maternal death, incidence of intrauterine growth retardation, preterm birth, ante- or postnatal asphyxia, low birthweight, neonatal infection, neonatal anaemia, required paediatric assistance, admission to neonatal ward, congenital malformations, foetal or neonatal death, GA at delivery, date of delivery and birthweight.

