### Participant timeline {13}

The participants will attend the baseline visit and 4 follow-up visits: *T*_3w_ 3 weeks (± 2 days), *T*_6w_ 6 weeks (± 3 days), *T*_12w_ 12 weeks (± 1 week), and *T*_18w_ 18 weeks (± 1 week) from baseline (see Figs. 1 and 2).

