## Statistical methods

### Statistical methods for primary and secondary outcomes {20a}

Time to Hb < 11 g/dL and proportion of participants with correction of anaemia (Hb ≥ 11.0 g/dL) at *T*_3w_, *T*_6w_, and *T*_12w_ will be estimated by a Kaplan-Meier curve using scheduled visits. Based on the Kaplan-Meier curve, the proportion of participants who have met the primary endpoint (achievement/maintenance of Hb ≥ 11 g/dL at all post-baseline visits) at *T*_18w_ will be estimated and compared between the treatment groups.

The primary endpoint analysis will be performed for the intention-to-treat analysis set and will be repeated for the full analysis set and per protocol analysis sets.

As sensitivity, the risk difference will be used to compare the proportion of participants with Hb ≥ 11 g/dL at all post-baseline visits. Risk difference and the associated 95% Newcombe CI and *p* value will be calculated, adjusting for strata (Hb </≥ 11 g/dL at inclusion) using the Cochran-Mantel-Haenszel method. In this analysis, participants who do not complete the study period will be set as failures.

The change in Hb and biochemical safety parameters from baseline to *T*_3w_, *T*_6w_, *T*_12w_, and *T*_18w_ will be analysed using a restricted maximum likelihood-based mixed model for repeated measures approach.

The proportion of participants who (a) receive an additional IV FDI dose, (b) receive allogenic RBC transfusions, (c) discontinue from the trial because of lack of response or intolerance of investigational drugs, and (d) develop hypophosphatemia will be compared between the treatment groups by Fisher’s exact test.

The number of units of RBC transfused per transfused participant from baseline to final subject visit will be compared between the treatment groups by an analysis of variance or Wilcoxon test.

For participants in the oral iron group, AEs with onset at/after the time of first additional IV iron isomaltoside dose will be excluded from the main AE summaries. In addition, displays of all AEs per overall treatment group will be produced, as well as summaries and participant listings of AEs occurring at/after the time of first additional IV iron isomaltoside dose.

Medical record follow-up will be tabulated by descriptive statistics.

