## Discussion

The objective of this study is to compare IV FDI to oral iron therapy for the prevention of IDA in iron-deficient pregnant women.

We use the first-choice treatment method as a comparator in our trial. Therefore, we will be able to use the study results for assessing the potential benefit of IV FDI in a clinical setting.

In the first approved version of our protocol, we aimed to recruit women with IDA. However, we soon discovered that IDA is rare in 1st and beginning of 2nd trimester in Danish women. Thus, to recruit pregnant women with IDA, we either would have to examine women in 3rd trimester or prepare for a very long enrolment period (i.e. a decade). At this point, it became clear that a preventive approach would be beneficial for both the pregnant women and for the progression of our trial. This resulted in a trial design aiming to prevent IDA, as opposed to treating IDA after manifestation. It is well known that IDA causes morbidity [14–22]. However, previous studies have focused on treatment [36–42]. We have focused on prevention, thereby minimising the damage that IDA can cause before effectively treated. From a clinical perspective, it makes good sense to avoid the development of morbidity rather than treating it, once occurred. IV iron treatment is more expensive than oral treatment, both because of the cost of the actual medicine, but also costs associated with administration. However, IV iron might correct ID faster and have higher compliance than oral treatment and thereby reduce complications at delivery (i.e. length of hospital admission, surgery, RBC transfusions), making this a highly relevant trial in a socioeconomic context as well.

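### RBC units are to be tested among transfused women only, a subset formed after randomisation; transfusions around delivery are recorded but not compared between arms

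*Protocol article*

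**What the plan says.** Objectives {7} names, as secondary objective (iv), the need for an extra IV dose or a rescue RBC transfusion. Outcomes {12} turns the transfusion part into two endpoints: the "number of participants receiving RBC transfusions and the number of RBC units per transfused participant from baseline to final subject visit".

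Statistical methods {20a} compares the proportion transfused by Fisher's exact test. For units it says: "The number of units of RBC transfused per transfused participant from baseline to final subject visit will be compared between the treatment groups", by analysis of variance or Wilcoxon test.

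On timing, women are "enrolled at gestational age (GA) 14 + 0–21 + 0", and the last visit in Participant timeline {13} is at "18 weeks (± 1 week) from baseline". Later events are covered in Outcomes {12}: "Specific explorative endpoints registered between final subject visit up until 7 days postpartum will be extracted from medical records". Blood transfusions are on that list. Statistical methods {20a} then states: "Medical record follow-up will be tabulated by descriptive statistics".

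The Discussion suggests that IV iron might correct iron deficiency faster, be better complied with, and so "reduce complications at delivery (i.e. length of hospital admission, surgery, RBC transfusions").

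**The concern.** There are two separate points.

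**Units.** Whether a woman is transfused may depend on her treatment. Comparing units only among transfused women compares two groups that randomisation did not form. If one treatment prevents mainly the small transfusions, the women still transfused in that arm are the heavier cases, and their mean rises although the arm as a whole received less blood. With very few transfusions, the test may also have nothing to work on.

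**Window.** Both tested transfusion endpoints close at the final subject visit. The transfusions that the Discussion has in mind are those at delivery, and these receive no between-arm estimate. A near-empty in-trial comparison could be reported as no difference in transfusion, and readers could carry that over to delivery.

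**Working it through.** **Inputs.** 100 women per arm (Sample size {14}); enrolment at GA 14+0 to 21+0 (Study setting {9}); last visit 18 weeks ± 1 week after baseline (Participant timeline {13}). The article gives no transfusion rate. I assume 0.5% to 1% per arm before the final visit, and wider values for power. A low rate is plausible because women meeting transfusion criteria are excluded (Eligibility criteria {10}) and IV iron is allowed in both arms for iron deficiency anaemia at weeks 6 and 12 ({11b}). Neither provision rules out transfusion for antepartum bleeding.

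**The plan's own figure.** The sample size rests on the primary endpoint only. With 5% vs 17.5%, two-sided 5%, 80% power and pooled variance:
n = [1.96·√(2·0.1125·0.8875) + 0.842·√(0.05·0.95 + 0.175·0.825)]² / 0.125² ≈ 99.1, so 100 per arm. This reproduces. No power is stated for transfusion.

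**Direction of the units comparison.** Suppose that under treatment A, a women need 1 unit each and b women need m > 1 units each. Suppose treatment B prevents the a small transfusions and nothing else.
- Units per transfused woman: A = (a + bm)/(a + b), which is less than m; B = m. B looks worse.
- Total units: A = a + bm; B = bm. B used less blood.

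Divided by all randomised women, the comparison has the right sign.

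**Whether the units test can be run.** With X ~ Binomial(100, p) in each arm:

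| p per arm | P(X ≥ 1) | at least 1 in both arms | P(X ≥ 2) | at least 2 in both arms |
|---|---|---|---|---|
| 0.5% | 1 − 0.995¹⁰⁰ = 0.394 | 0.394² = 0.16 | 0.090 | 0.01 |
| 1% | 1 − 0.99¹⁰⁰ = 0.634 | 0.634² = 0.40 | 0.264 | 0.07 |

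So with probability 0.60 to 0.84 at least one arm has no transfused woman and there is nothing to compare. Two per arm is the least that gives a variance in each arm. Even then, an exact two-sided Wilcoxon test of 2 vs 2 cannot go below 2/6 = 0.33.

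**Window.** GA at the last visit is 14+0 + 18 = 32+0 to 21+0 + 18 = 39+0 nominally, and 31+0 to 40+0 with the ± 1 week.

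**Proportion transfused.** Two-sided Fisher p-values at 100 per arm are 0.059 for 5 vs 0 and 0.029 for 6 vs 0, so at least 6 vs 0 is needed. Power under assumed rates (oral vs IV):

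| Rates | Power |
|---|---|
| 2% vs 1% | 0.6% |
| 3% vs 1% | 3.4% |
| 5% vs 2% | 9.6% |

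These figures apply equally to a window that includes delivery, if its rates lie in this range.

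**What 0 vs 0 would show.** The Wilson upper limit for 0/100 is 1.96²/(100 + 1.96²) = 3.84/103.84 = 3.7%. The Newcombe 95% interval for the difference is then −3.7 to +3.7 percentage points, which is wide for an event this rare.

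**The case against.** A reader might infer something stronger: that the endpoints stop before almost all deliveries, and that the trial therefore cannot address a transfusion benefit it claims. The document does not support this.

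- **No benefit is claimed.** The Discussion sentence says only that IV iron might have this effect. The stated objective is rescue transfusion, paired with the extra IV dose, and the in-trial window suits it.
- **The share of deliveries is not documented.** No distribution of enrolment GA or delivery date is given, and for women enrolled at 21+0 the last visit can be as late as 40+0. The article does register labour and delivery events after the final visit, so it expects delivery there, but that does not establish almost all.
- **Delivery transfusions are handled openly.** They are collected, named as explorative and tabulated. Describing rare events without a test is legitimate.
- **Only the units endpoint is conditional.** The number of women transfused is compared over the randomised groups.
- **Ending the test at the final visit has a reason.** Other iron is prohibited during the trial ({11d}). Afterwards women return to standard antenatal care, where both treatments are available ({30}).
- **A longer window does not bring adequate power**, as the figures above show.

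All of this stands, and it is why the in-trial endpoint should stay. None of it rescues the units test, whose fault lies in the choice of denominator and not in the window or the sample size.

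**Conclusion.** The test of units per transfused woman should not be a between-arm comparison. That follows from its definition and needs no assumed rate. That it may also be uncomputable does rest on an assumption, 0.5% to 1% transfused per arm, under which two or more transfused women in both arms has probability 0.01 to 0.07.

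The window is a smaller matter. It is a defensible choice for objective (iv), but it leaves the delivery effect suggested in the Discussion without a between-arm estimate, although the data for one are already extracted. I take the final subject visit to be the week-18 visit for women who complete the trial; the article does not define it separately.

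The primary endpoint and the sample size are not affected.

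**What to change.** 1. **Units.** Replace the tested endpoint by total RBC units per randomised woman up to the final visit, zeros included, analysed as randomised. List units in transfused women by arm, descriptively only.
2. **In-trial transfusion.** Keep the proportion transfused up to the final visit, with Fisher's test, for objective (iv).
3. **Delivery.** Add a supplementary risk difference with 95% confidence interval for any RBC transfusion from randomisation to 7 days postpartum, joining trial-visit and medical-record data. The Newcombe interval already planned for the primary sensitivity analysis stays defined with zero events. Check that the record extraction identifies RBC transfusions, since the explorative list says only blood transfusions.
4. **Wording.** State that power is low and that absence of a difference is not evidence of equivalence.

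The cost is wording and a little programming; the plan already provides for collecting both data sources. Three limits need stating: women lost before delivery lack the later part, iron treatment after the final visit is outside protocol control, and the estimate will be imprecise. Because the trial is open-label with unblinded analysts ({17a}), the change should be fixed before outcome data are examined by arm.

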### Adverse event reporting and harms {22}

AEs are collected and evaluated for relatedness to trial drug, seriousness, severity, expectedness, and outcome. AE are defined in the ICH-GCP guideline.

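### The highlighted symptomatic safety endpoints are uneven: hypersensitivity counts only when serious or severe, while nine oral-iron-type events carry no severity limit (minor)

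*Protocol article*

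**What the plan says.** Safety is one of the secondary objectives on which the two treatments are to be compared (Objectives {7}, item v). Outcomes {12} then names the safety endpoints in one long sentence. Three of them concern adverse events in the mother:

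- all adverse events: "type and incidence of AEs observed at any time until final subject visit";
- hypersensitivity: "serious or severe hypersensitivity reaction starting at or after the first dose of randomised treatment";
- a special-interest list: "AEs of special interest (constipation, diarrhoea, flatulence, nausea, vomiting, abdominal pain, dyspepsia, dysgeusia, and stool discoloration".

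The second and third follow one another directly: "serious or severe hypersensitivity reaction starting at or after the first dose of randomised treatment, AEs of special interest (constipation, diarrhoea".

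The same sentence also names hypophosphatemia (a laboratory cut-off of 2 mg/dL), discontinuation for lack of response or intolerance, foetal bradycardia related to an IV infusion at or after gestational week 26, and change in biochemical safety parameters.

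On the oral comparator, the Background states: "Oral iron supplementation is associated with gastrointestinal adverse effects, affecting patient compliance". Adverse event reporting and harms {22} adds: "AEs are collected and evaluated for relatedness to trial drug, seriousness, severity, expectedness, and outcome".

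Statistical methods {20a} gives a between-group test for hypophosphatemia and for discontinuation (Fisher's exact test). It gives none for the special-interest events or for hypersensitivity. The trial is open label, with neither outcome assessors nor analysts blinded (Who will be blinded {17a}).

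**The concern.** Adjacent endpoints are built to different rules. The events typical of oral iron are singled out with no stated severity limit. The symptomatic reaction typical of an IV iron is singled out only in its serious or severe form, and ordinary infusion-related or infusion-site reactions are not singled out at all. A mild bout of constipation enters a highlighted list; a mild or moderate reaction to the infusion does not.

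What is at stake is how the tolerability result reads. Adverse events are among the key secondary results to be posted publicly (Dissemination plans {31a}), and the trial is open label and run by the manufacturer of the IV product. If a summary of maternal symptoms rests on the two highlighted endpoints alone, part of any advantage for the IV product would come from how they were defined. Eligibility criteria {10} also exclude women with previous hypersensitivity to IV iron or with "active asthma within the last 5 years; multiple allergies". That is understandable as a precaution, but it can be expected to make serious or severe reactions rarer still.

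**Working it through.** **The plan's own figure.** No safety endpoint carries a stated rate or precision. The only figure that matters here is the arm size from Sample size {14}: 5% against 17.5% with low haemoglobin, 5% significance level, 80% power, 100 per arm. With pooled variance, a two-sided test and a mean proportion of (0.95 + 0.825)/2 = 0.8875:

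n = [1.960 × √(2 × 0.8875 × 0.1125) + 0.842 × √(0.95 × 0.05 + 0.825 × 0.175)]² / 0.125² = 99.1, rounded up to 100.

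The figure reproduces (power 80.3% at 100 per arm). It is used below only as the denominator.

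**The named endpoints side by side.**

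| Endpoint in Outcomes {12} | Severity condition | Typical of |
|---|---|---|
| All adverse events by type | none | either drug |
| Nine special-interest events (eight gastrointestinal, plus dysgeusia) | none stated | oral iron, per the Background |
| Hypersensitivity | serious or severe | IV iron |
| Infusion-related or infusion-site reactions | no group named | IV iron |
| Hypophosphatemia | laboratory cut-off only | laboratory finding, compared by a stated test |
| Foetal bradycardia | related to infusion, week 26 or later | IV iron |
| Discontinuation for lack of response or intolerance | none | either drug |

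Among the rows for specific maternal symptoms, only hypersensitivity is filtered by severity. That the nine events count at any grade is inferred from silence, but the neighbouring item states a threshold explicitly, so the inference is a fair one.

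**Timing of the bradycardia endpoint.** The baseline infusion is given at 14 + 0 to 21 + 0 weeks, so an endpoint starting at week 26 cannot record it. Additional doses are allowed at 6 and 12 weeks, nominally weeks 20 to 27 and 26 to 33, and in both arms. The endpoint can therefore arise only from an additional dose, and possibly in a woman randomised to oral iron.

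**How much the thresholded endpoint can show.** The documents give no rates, so those below are assumptions. The chance of no event in 100 women at true rate r is (1 − r)^100:

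- r = 0.1%: 0.905
- r = 0.3%: 0.740
- r = 1%: 0.366

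If 0 of 100 are seen, the upper 95% limit is 1 − 0.05^(1/100) = 2.95% one-sided, or 1 − 0.025^(1/100) = 3.62% as the upper end of a two-sided interval.

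As an illustration of comparative information, Fisher's exact test with 100 per arm and none on oral iron gives p = 0.059 for 5 against 0 and p = 0.029 for 6 against 0. At least 6 events are needed for p < 0.05. The chance of 6 or more in 100 is:

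- 0.05% at a true rate of 1%
- 38% at 5%
- 94% at 10%

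If milder reactions occur in 3% to 10% of women (assumed), that is 3 to 10 of 100 without a grouped count. At the upper part of that range a group of any grade could show a difference that the thresholded endpoint could not.

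**The case against.** The strongest reply is that nothing is lost. The all-adverse-event endpoint stands in the same sentence with no severity limit, and relatedness, seriousness and severity are assessed for adverse events. Milder reactions are therefore recorded within a named endpoint and can be shown by type, grade and arm. This stands: the gap is the absence of a grouped, highlighted count, not the absence of data.

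A reader might go further and infer that milder reactions enter no endpoint, or that the safety comparison can show little except an excess on oral iron. The document supports neither reading. Hypophosphatemia has a formal between-group test, discontinuation for intolerance applies to both drugs, and infusion-related foetal bradycardia can be caused only by the IV product. In addition, Statistical methods {20a} removes adverse events after an additional IV dose from the main summaries for the oral arm only. That lowers the oral arm's count there, although displays of all events by overall group are also planned.

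Other replies also carry weight:

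- The nine events are counted in both arms and have no stated test. The Discussion itself describes nausea as a pregnancy symptom.
- Grouping of terms and table layout are commonly left to the analysis plan, which is not shown. It may already contain such a group.
- The Background's remark, "Overall hypersensitivity reactions were rare", concerns another IV iron in women who already had anaemia. It supplies no rate for this trial.
- The zero-event arithmetic mainly shows that rare events are rarely seen in 100 women. It does not measure any tilt.

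None of this removes the difference in thresholds between the two highlighted maternal endpoints. Of the other endpoints, hypophosphatemia is a laboratory finding, bradycardia is a foetal one, and discontinuation does not count a reaction after which the woman stays in the trial.

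**Conclusion.** The point holds in limited form and is minor. The named maternal symptom endpoints apply a severity threshold to hypersensitivity and none to the nine oral-iron-type events, and no group covers infusion-related or infusion-site reactions. The highlighted symptomatic tolerability comparison is therefore uneven between the drugs. Safety as a whole is not one-sided.

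The size cannot be fixed from the documents. Under the assumed rates, the hypersensitivity endpoint would show no event in the IV arm with probability 37% to 90%, and 3 to 10 women with milder reactions would have no grouped count. The conclusion rests on reading the absence of a severity limit on the nine events as any grade, and it falls away if the analysis plan already defines a matching group. No stated test, the primary analysis or the sample size is affected.

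**What to change.** Before analysis, name a further group beside the special-interest events: hypersensitivity and infusion-related or infusion-site reactions of any grade. Fix its list of terms in writing without reference to the results, since the analysts are not blinded. Tabulate it by arm next to the nine events, with the same grade breakdown and the same handling of events after an additional IV dose. Keep serious or severe hypersensitivity as a subset, so the present endpoint is still reported. State explicitly that the nine events are counted at any grade, if that is what is meant.

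The cost is one more table and a few lines of text. No new data or visits are needed, because adverse events are already collected with severity and relatedness. The one drawback is that the ferric derisomaltose profile may look slightly less favourable than under the present endpoints.
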